## Methods/design

The ENHANCE study is an open two-arm parallel-group randomised controlled trial. This is a superiority trial to determine if there is a clinically relevant difference between exercise and behaviour change counselling versus usual care. The 12-week ENHANCE programme is delivered to trial participants by an accredited exercise physiologist (AEP) in a university exercise physiology clinic. Minimum training at this level is a bachelor’s degree in sports science (kinesiology) and a professional honours qualification (4.5 years total full-time study at a tertiary institution). Data are collected at baseline and 26 weeks, and at 26 weeks post-surgery. A schematic diagram of enrolment is shown in Fig. 1.

**Fig. 1 Fig1:**
[figure not shown]
SPIRIT figure of the ENHANCE study protocol. SF-12 Short Form 12-item health survey on medical outcomes

### Setting

The study is conducted in Australia at Launceston, Tasmania. The ENHANCE programme is delivered in an exercise physiology clinic at a major university.

### Inclusion criteria

To be eligible to participate in the trial, patients have to meet the following criteria: new and existing patients on the surgery waiting list (<6 months on list), aged 80 years and younger (due to older people being less mobile and more sedentary and having more comorbidities and poorer cognition), able to read and understand English, willing to participate in a 12-week exercise intervention and provide informed consent.

### Exclusion criteria

Patients will be ineligible to participate in the trial if they meet one or more of the following criteria: an unstable medical condition whereby participation in exercise may present an additional health risk as determined by the consulting surgeon, prior diagnosis of a progressive neurological condition (e.g., Parkinson’s disease) or confined to a wheelchair.

Eligible participants will be invited by a nurse researcher attached to the Launceston General Hospital Orthopaedic Services to participate in the study. They will be provided with an information package and consent form. Potential participants will be provided with further information by a researcher who is an AEP. The AEP will also conduct additional clinically relevant screening of potential participants for conditions that could be made worse by exercise. Participants do not receive any incentives.

### Development of the ENHANCE programme

The development of the ENHANCE programme has followed a two-stage process and is informed by the HAPA. First, international guidelines on the development of exercise interventions for adults waiting for hip or knee surgery were reviewed. These guidelines recommend that exercise interventions for people with OA should be multi-dimensional and include exercise to improve whole-body muscle strength, mobility and aerobic capacity. It was, therefore, determined that including participants with both hip and knee arthroplasty widens the applicability of this trial, especially as the current activity levels for both cohorts are similar following arthroplasty.

Second, a series of interviews with people with OA and experienced health-care professionals was conducted. A draft intervention was then produced, which was refined by expert consensus.

### Description of the intervention

The ENHANCE programme is a 12-week programme consisting of 24 group classes of progressive exercise intervention combined with five group counselling sessions, delivered after the exercise class. Groups will commence and continue as discrete groups with a maximum of five participants per group. The classes are run twice a week for 60 min each. All sessions are delivered by an AEP. In accordance with recent recommendations for chronic disease management and physical activity guidelines, the intervention is stage-adapted and participants are encouraged to exercise within their own capabilities, which depend on individual symptomatology. Participants in the intervention group also receive an ENHANCE workbook, which includes printed material tailored for people with OA and informed by the principles of HAPA. The workbook was developed by the research team (Additional file 1) and includes general information about the benefits of exercise, setting goals, forming habits and making plans. The booklet describes various activities, which are either scheduled as part of the behaviour counselling face-to-face sessions or are reflective activities for participants to complete at home.

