### Sample size

The sample size has been determined to be 50 patients in each group to detect an increase of 1200 (24%) daily steps (alpha 0.05, power 0.8) based on research indicating usual changes in step count after lower limb joint replacement [10]. The study that our sample size calculations are based upon experienced a low withdrawal rate of 4%. We have made a conservative estimate of a 10% withdrawal rate and, hence, will recruit 110 participants.

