### Data analysis

Differences in primary and secondary outcomes between groups will be compared using an intention-to-treat analysis. Once a participant is randomised to a study group, they will be considered a trial participant and analysed according to their allocated group, regardless of missing data for follow-ups or the amount of intervention received. Bivariate relationships will be tested with Pearson or Spearman correlations, independent *t*-tests or Mann–Whitney *U* tests (to examine relationships between the dependent variables and the independent variables) or chi squared tests for categorical variables. Each primary and secondary outcome will be analysed using a two-way repeated-measures analysis of covariance (ANCOVA) to determine differences between groups (exercise versus usual care) and between time points (test 1, test 2 and test 3). In addition, effects of the intervention targeting the psychological HAPA-based constructs on regular exercise is tested along with the key processes (mediation) involved. Data will be analysed with a linear mixed model with condition as between-participants effects and time points as within-participants effects. A path analysis will be used to determine mediation effects. Data analysis will be performed using statistical software STATA (STATA 13, Stata Corp, College Station, TX, USA) and Mplus. Statistical significance is set at *p* < 0.05 for all analyses.

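### Exercise groups of up to five form clusters in the intervention arm only, and neither the stated sample size nor the stated models allow for them

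*Protocol article*

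**What the plan says.** Under Description of the intervention, the programme is 24 group classes and five group counselling sessions, and "Groups will commence and continue as discrete groups with a maximum of five participants per group". Under Usual care, controls receive a brochure and their ordinary care, with no grouping. Under Programme adherence, intervention participants are placed in classes by starting date and availability.

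The Sample size section states: "The sample size has been determined to be 50 patients in each group", "to detect an increase of 1200 (24%) daily steps", with "alpha 0.05, power 0.8". The source is described as "based on research indicating usual changes in step count after lower limb joint replacement". No SD, ICC or design effect appears.

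The Data analysis section names a two-way repeated-measures ANCOVA (arm by test 1, test 2 and test 3) for every primary and secondary outcome. It then says: "Data will be analysed with a linear mixed model with condition as between-participants effects and time points as within-participants effects". Neither model has an exercise-group term.

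**The concern.** Members of one exercise group share a start date, a timetable and 29 scheduled group activities (24 classes plus five counselling sessions). The counselling table includes a session on sharing success stories and one that covers social support. The table of intervention components lists modelling by others as a technique. These are reasons to expect that outcomes within a group may be positively correlated. Controls have no such structure.

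The stated models handle repeated measurements within a person but treat different people as independent. Where the correlation is positive, the intervention-arm mean is less precise than such an analysis assumes. Confidence intervals are then too narrow, p-values too small, and a power figure based on independent participants is too high. False-positive findings of a difference become more likely than the stated 5%.

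**Working it through.** **Inputs from the protocol article.** Difference 1200 steps per day, alpha 0.05, power 0.8, 50 per arm (Sample size); group size m of at most 5 (Description of the intervention).

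**Assumptions.** Two-sided test; all groups of exactly five, so 50/5 = 10 groups; equal total variance in both arms; ICC from 0.01 to 0.10.

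**Step 1: the plan's own figure.** No SD is stated, so 50 per arm cannot be reproduced independently. It can only be solved backwards:

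SD = 1200 / [√(2/50) × (1.960 + 0.842)] = 1200 / (0.2 × 2.802) ≈ 2142 steps.

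Using the t-test instead gives about 2121. By construction, power at ICC 0 is then 80%.

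**Step 2: formulas.** Only the intervention arm is clustered:

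- Design effect in that arm: DE = 1 + (m − 1) × ICC.
- True standard error of the difference: SD × √[(1 + DE)/50].
- Ratio of true to assumed standard error: R = √[(1 + DE)/2].
- Type I error of the test that ignores groups: 2 × [1 − Φ(1.960/R)].
- Power of a test with the correct standard error: Φ(1200/true SE − 1.960).

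Worked example at ICC 0.05: DE = 1 + 4 × 0.05 = 1.20. R = √(2.20/2) = 1.049. Type I error = 2 × [1 − Φ(1.869)] = 6.2%. True SE = 2142 × √(2.20/50) = 449. Power = Φ(1200/449 − 1.960) = Φ(0.711) = 76.2%.

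**Step 3: results, m = 5, SD 2142, 50 per arm.**

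| Assumed ICC | DE | R | Type I error, groups ignored | Power, normal approximation | Power, Satterthwaite df from 10 groups |
|---|---|---|---|---|---|
| 0.01 | 1.04 | 1.01 | 5.2% | 79.2% | not computed |
| 0.02 | 1.08 | 1.02 | 5.5% | 78.4% | 75.6% |
| 0.05 | 1.20 | 1.05 | 6.2% | 76.2% | 73.1% |
| 0.10 | 1.40 | 1.10 | 7.4% | 72.5% | 69.0% |

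The last column uses df = (v₁ + v₀)² / (v₁²/9 + v₀²/49), with v₁ = DE/50 and v₀ = 1/50. This gives df of about 28.8, 26.8 and 24.2 at ICC 0.02, 0.05 and 0.10. Part of the fall in that column therefore comes from the few degrees of freedom: at ICC 0.05, 76.2 − 73.1 = 3.1 points.

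**Step 4: sensitivity to group size.** With m = 3 and ICC 0.05, DE = 1.10, type I error is 5.6% and power is 78.1%.

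**Step 5: sensitivity to baseline adjustment.** If 2121 is a raw SD and the baseline value correlates ρ with follow-up (ρ is an assumption), the residual SD is 2121 × √(1 − ρ²). With ρ = 0.5 this is 1837. Applying the same ICC to the residuals, with m = 5 and Satterthwaite df, power is about 85% at ICC 0.05 and 82% at ICC 0.10. With ρ = 0.3 and ICC 0.05 it is about 78%. The ratio R depends only on DE, so the standard error is still understated by the same factor if groups are ignored.

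**The case against.** The strongest reply has five parts.

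- **No ICC is given, and the effect may be small.** This stands. At 0.01 to 0.02 the type I error is 5.2% to 5.5% and the normal-approximation power loss is under two points. Exercise prescriptions, goals and action plans are individual. Follow-up at 26 weeks falls well after the 12-week programme, and the last assessment is 26 weeks after surgery, so any group effect may have faded.
- **Five is a maximum.** This stands; smaller groups shrink the effect.
- **Power may be preserved.** A reader might infer that the trial does not have its stated power. The document does not support that. It gives no SD, and the planned covariance analysis could offset some or all of the loss if baseline predicts follow-up well enough. Only a narrower statement holds: the 0.8 contains no allowance for clustering.
- **Not every outcome need be affected.** A reader might also infer that all p-values in the trial are too optimistic. The outcomes run from step count to HbA1c and waist circumference, and one ICC need not apply to all. The statement is conditional on positive correlation for the outcome in question.
- **Random effects are often left to an analysis plan.** This has limited force. The article names its models and the effects in them, and it gives a power figure with no design effect. The mixed-model sentence may concern only the psychological constructs, but the ANCOVA named for primary and secondary outcomes has no group term either.

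**Conclusion.** The concern holds in conditional form. The design is partially nested, and the stated sample size and models do not allow for exercise group. For any positive ICC the standard error of the treatment comparison is understated. With groups of five, the understatement is about 1% at ICC 0.01 and about 10% at ICC 0.10, and the true level of a nominal 5% test runs from 5.2% to 7.4%. Unadjusted power runs from about 79% down to 73% by normal approximation, and lower with degrees of freedom based on 10 groups.

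These figures rest on an assumed ICC, an SD solved back from the plan's own power, and groups at their maximum size. The effect is small at the low end of the range and material from about ICC 0.05. This is a should-fix point.

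**What to change.** 1. Record the exercise-group identifier for each intervention participant. Attendance sheets are already planned for the classes.
2. Analyse test 2 and test 3 as outcomes, with the test 1 value as covariate, in a partially nested mixed model: a random effect for exercise group in the intervention arm only, a participant random effect, and Satterthwaite or Kenward-Roger degrees of freedom.
3. If test 1 stays in the outcome vector, let the group random effect act only after baseline. A time-constant group intercept u would impose clustering before any class has met. It would also largely cancel from the arm-by-time contrast, since (y₂ + u) − (y₁ + u) = y₂ − y₁, and so leave the standard error uncorrected.
4. State the SD behind the 50 per arm, and report power at that size over an ICC of 0.01 to 0.10 in place of a single 0.8.

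The cost is one identifier, one variance component, slightly wider intervals and a less favourable stated power. No new patients are needed if the sponsor accepts the restated power. By the unadjusted normal approximation with groups of five, restoring 80% would take 25 × (1 + DE) per arm: 25 × 2.20 = 55 at ICC 0.05 and 25 × 2.40 = 60 at ICC 0.10. The article describes the trial as ongoing; if that still holds, the model can be settled before the data are analysed.

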#### Exercise programme

The exercise programme will be individualised based on the assessment at entry by an AEP who has experience in the delivery of exercise to people with chronic health conditions. The intensity and progression of exercises will be determined on an as-needs basis and will include both the class-based programme and home-based exercises. The required elements of the exercise programme will be based on clinical evidence for hip and knee OA [23] and are outlined in Table 1. The dose will be determined by the supervising AEP in negotiation with each participant’s preferences and clinical status.

**Table 1 Tab1:** Exercise components

Exercise component	Supervised (twice weekly)	Unsupervised (home)
Aerobic component	40–60% HR max, 12–14 repetitions; walking, cycling or arm ergometry	Low to moderate intensity (40–60% HR max, 12–14 repetitions); a home programme aiming to accumulate 20–30 min a day for 2–5 days a week will be progressively introduced where safe and practical
Flexibility: static stretching	Building to 3–5 stretches of up to 30 s duration	Initially, once daily at home to comfortable end of range (up to 15 s holds)
Strengthening isometric exercises	40% MVC with up to 10 holds for up to 6 s	Where safe and practical, this will be expanded to the home exercise programme and repeated daily
Strengthening isotonic exercises with TheraBands	40% MVC up to 15 repetitions	Will commence at low levels (40% MVC with between 10 and 15 repetitions) and progress when possible to higher loads and fewer repetitions to stimulate strength gains; once weekly

*HR max* maximum heart rate, *MVC* maximal voluntary contraction

The AEP will regularly review participants’ original or amended goals, participation in their home exercise programme since the previous class, barriers experienced, motivation for exercise, recent symptoms and pain status. Attendance and adverse events will be documented.

#### Behaviour change counselling programme

Behaviour change strategies and the principles of the counselling component of the intervention are guided by HAPA. The principles are designed to increase self-efficacy for exercise and management of other OA-related symptoms as well as improving the ongoing participation in positive health behaviours. Table 2 presents the content of the five behaviour counselling sessions, which are delivered as exercise coaching group sessions. Each session has a certain topic, matched with the mode of consultation. Face-to-face counselling sessions deal with the topics ‘Why is exercise good for me?’, ‘Building confidence’, ‘Creating plans and habits’, ‘Staying in control’ and ‘Visualising the future’. Behaviour change methods emphasised in this intervention include self-monitoring, goal setting, positive reinforcement, positive self-talk, self-reward, motivational advice and relapse prevention coaching. Over the 12 weeks, the HAPA-based intervention will comprise key components that map behaviour change techniques onto specific HAPA psychological constructs, drawn from theoretical and empirical evidence. Table 3 provides the theoretical foundation for the proposed HAPA-based intervention, outlining key components, potential behaviour change techniques and potential mediators.

**Table 2 Tab2:** Overview of the behavioural counselling components of the ENHANCE intervention

Session	1	2	3	4	5
Intervention week	1	2	3	6	12
Main topic	Why is exercise good for me?	Building confidence	Creating plans and habits	Staying in control	Visualising the future
Theoretical aspects	General health benefits of physical activity and recommendations for enhancing physical activity Goal setting for the end of the intervention Organisational aspects of the programme Begin exercising hints and safety tips	Previous success stories Sharing success stories	Goal setting, action planning and coping for the following week	Identification of individual barriers to and resources for physical activity (significance of social support) Strategies for dealing with barriers	Goal setting, action planning and coping for the future post-surgery

**Table 3 Tab3:** Proposed HAPA-based intervention components, behaviour change techniques, and potential mediators

Intervention components	Behaviour change techniques	Potential mediators
Motivational component		
Providing information on the risk factors of a sedentary lifestyle	Information provision Mental imagery	Risk perception
Providing information on the benefits and advantages of regular walking	Information provision Mental imagery	Positive outcome expectancy
Establishing confidence to start regular walking	Identification of resources Modelling (modelling by others) Mental imagery Verbal persuasion	Action self-efficacy
Formulating the intentions of regular walking	Intention formation Goal setting	Intention
Volitional component		
Making plans on when, where, how and with whom to conduct regular walking	Planning exercise	Action planning
Developing strategies to cope with the barriers that may interfere with regular walking	Identification of barriers Problem-solving	Coping planning
Developing confidence in maintaining regular walking with barriers, as well as resuming regular walking if interrupted	Mental imagery Mastery experience (past experience)	Maintenance self- efficacy Recovery self-efficacy
Developing strategies to remind and monitor regular walking	Self-monitoring exercise Reminders and sign-in table	Action control

*HAPA* Health Action Process Approach

Participants work with the AEP to identify small, gradual changes to exercise patterns that can be mastered and maintained, rather than drastic changes that are less likely to be maintained over time. This facilitates a sense of mastery and confidence, which can be built upon throughout the intervention to build self-efficacy. Each intervention contact results in a behaviourally specific action plan that specifies exactly what the participant intends to do and when. Also in the contact sessions, barriers and supports are identified, confidence is assessed and problem-solving is discussed as necessary. These steps are repeated during intervention counselling sessions, with goals being adjusted as necessary. Participants are encouraged to set their own goals based on their fitness level and circumstances.

### Usual care

Participants in the control group receive a generic information brochure at their baseline assessment point, *Arthritis (osteoarthritis) and exercise*, produced by Exercise is Medicine Australia [24]. Otherwise, participants allocated to usual care receive their concomitant care while they are on the surgical waiting list, attending for ENHANCE assessments at 6 months after baseline and at 6 months after their surgery.

### Sample size

The sample size has been determined to be 50 patients in each group to detect an increase of 1200 (24%) daily steps (alpha 0.05, power 0.8) based on research indicating usual changes in step count after lower limb joint replacement [10]. The study that our sample size calculations are based upon experienced a low withdrawal rate of 4%. We have made a conservative estimate of a 10% withdrawal rate and, hence, will recruit 110 participants.

### Randomisation

After completing all baseline data collection measures, participants are randomised to either the intervention group or the control group. Participants in the intervention group receive evidence-based physical activity guidelines supervised by an AEP for the 12 weeks. In addition, those in the intervention group receive an instructor-developed exercise booklet, along with innovative counselling classes five times directly after their exercise session. Participants in the control group will receive an information sheet with general advice on the benefits of physical activity for adults with OA. Participants in either group may receive relevant concomitant care and interventions.

The randomisation schedule has been prepared by a researcher independent of the research project using a computer-generated random number table. To conceal randomisation, the independent researcher has prepared consecutively numbered, sealed, opaque envelopes, which are kept in a locked location. As ENHANCE is an exercise intervention, blinding of the participants and the researchers who conduct the exercise sessions is not possible. Outcome assessors will not be involved in the delivery of the intervention and will be blinded to group allocations.

### Assessment

All staff at the trial site have been trained in the study protocol and the procedures for collecting informed consent and assessment data. A data collection training manual has been developed to guide research staff in the administration of the informed consent and data collection procedures. Assessments are completed in person at baseline, at 26 weeks and at 26 weeks post-surgery (Fig. 1). Once the data have been entered into the local database, they will be transferred to the data manager for the trial, who will compare the hard copies with the database to check accuracy. The data manager will check all the primary outcome variables and a randomly chosen 20% of the other variables. If there are any errors in the primary outcomes, or more than 1% errors for other variables, all data will be checked. The database will not include the assigned treatments. These will be recorded in a separate database, so that the statistician analysing the data will remain blind to treatment allocation.

Potential participants complete a brief screening by telephone conducted by the research nurse. During the screen, an in-person baseline assessment is scheduled for eligible participants. Informed consent is obtained before the assessment. All questionnaires are administered by an interviewer. All baseline and follow-up assessments will be conducted at the intervention site.

All assessment sessions (baseline [time 1], week 26 [time 2] and 26 weeks post-surgery [time 3]) will include a measurement of the primary and secondary outcomes. An ENHANCE questionnaire on data related to the HAPA constructs and a range of dimensions related to health outcomes will also be administered (see Table 2). The baseline assessment will collect additional demographic information related to health, medical history and general health status.

